#### Methods of analysis to handle protocol nonadherence and any statistical methods to handle missing data

Cases of violation of the concomitant use of prohibited medications will be included in the FAS but not in the PPS. Postprandial data of blood glucose, C-peptide, active glucagon-like peptide-1, and total bile acids are not included in the FAS and PPS because they are significantly less reliable. Missing data are treated as missing data and will not be complemented.

#### Plans to provide access to the full protocol, participant-level data, and statistical code

Access to the datasets used and analyzed during the study is available in a fully anonymized form from the sponsor upon reasonable request.

### Oversight and monitoring

#### Composition of the coordinating center and trial steering committee

The research office will assist the principal investigator in the management and supervision of the study from medical, scientific, and ethical perspectives and will liaise with the parties involved in the conduct of the study.

#### Composition of the data monitoring committee, its role, and reporting structure

The data monitoring committee consists of research investigators and statistical analysts. The handling of data deviating from the study design and the handling of missing data will be evaluated in a blinded manner prior to analysis to determine the handling of all data.

#### Reporting of adverse events and harms

The incidence of diseases and adverse events will be used as a safety measure. These events will be recorded using CRF throughout the observation period. The analysis will be conducted using a safety analysis population after data fixation. Any unfavorable medical event that occurs to a research participant during the course of this study, including an exacerbation of previous illnesses, will be treated as an “adverse event.” Worsening of diabetes-related macrovascular and microvascular complications at the time of initiation of medication will also be treated as an adverse event. In this study, if the data related outcomes, including primary endpoints, secondary endpoints and exploratory endpoints, worsens, it will not be treated as an adverse event. When an adverse event will be observed, researchers will immediately take appropriate measures and report necessary information. If administration of BBG9-1 is discontinued or treatment for an adverse event becomes necessary, the researchers will inform the research participant.

If an adverse event occurs, the name, timing, degree, severity, outcome, date of confirmation of the outcome, relevance to the study, reason for judgment, suspect medication(s), treatment of the suspect medication(s), and other treatment details shall be recorded in the CRF. In principle, symptoms observed during the study will be followed-up until they normalize or recover to a level not considered an adverse event, or until symptoms stabilize or will be fixed in the case of irreversible adverse events due to organic damage.

The degree of adverse events will be classified according to the following criteria: mild, not detrimental to daily life; moderate, interference with daily life but only to the extent that activities can be performed with considerable patience; severe, to the extent that it significantly interferes with the performance of daily activities.

The outcome of adverse events will be classified according to the following criteria: recovery, recovery to a level that is normalized or not considered an adverse event; slightly relieved, symptoms have lessened but have not normalized; unrecovered, symptoms have not yet normalized at the time of the event; recovered but with residual aftereffects, recovered but still dysfunctional to the extent that it interferes with daily life; death; unknown, the outcome is unknown due to interruption of hospital visits.

Relevance to this study will be judged “not related” or “related” according to the following relevance criteria: the condition of the research participant; the time relationship with the treatment; the possibility of other factors.

A serious adverse event (SAE) is defined as any unwanted or unintended sign, symptom, or illness for a research participant, which is causally related to the research drug and corresponds to the following: 1) death, 2) life-threatening, 3) requires hospitalization or prolonged hospitalization for treatment, 4) results in permanent or significant disability or dysfunction, 5) the patient suffers from any other medically significant condition, 6) cases that are as serious as those listed in 1) to 5), and 7) congenital disease or abnormality in later generations.

If SAE occurs, the researchers will promptly take the necessary treatment, and regardless of the causal relationship between the SAE and the investigational drug in this study, the researchers shall report to the data center within 15 calendar days of becoming aware of the SAE, in accordance with the procedures of the institution. The data center will immediately summarize and report it to the administrator of the medical institution. The data center will immediately compile information, obtain instructions from the researchers, and report it to the research fund contributor (Biofermin Pharmaceutical Co., Ltd.). In the event of an adverse event other than an SAE, an adverse event will be noted in the CRF and reported to the data center upon submission of the CRF. The data center shall compile such information as appropriate, report it to the investigators and researchers, and receive corresponding instructions. The data center will also report the information to the research fund contributor (Biofermin Pharmaceutical Co., Ltd.), as appropriate. If new information concerning this research is obtained, the researchers will provide additional explanations to the participants and revise the consent and explanation documents as necessary.

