#### Outcomes

The primary endpoint of this trial will be the change in the total GSRS score from baseline to follow-up examination (12 ± 3 weeks after baseline examination). Secondary endpoints of this trial will be as follows: (1) change and percent change in following parameters from baseline to follow-up examination: GSRS subdomain scores, fecal properties/Bristol stool form scale, defecation frequency, blood test biomarkers (total bile acid, glycoalbumin, glucagon-like peptide-1, glucose-dependent insulinotropic polypeptide, glucagon, HbA1c, fasting plasma glucose, C-peptide, AST, ALT, gamma-glutamyltransferase, total cholesterol, high-density lipoprotein cholesterol, low-density lipoprotein cholesterol, triglycerides, blood urea nitrogen, and creatinine), physical examination (body weight and body mass index), urinary albumin creatinine ratio, gut microbiota (type of enterobacteria, relative abundance, alpha diversity, and beta diversity), macronutrients (total energy, carbohydrate, fat, protein, and dietary fiber intakes measured by brief-type self-administered diet history questionnaire [BDHQ]) [16]; (2) proportion of participants whose fecal property of Bristol stool form scale is within normal range (3.5–4.5); (3) medication adherence to the BBG9-1; (4) factors that affect GSRS total score or constipation/diarrhea subdomain scores; (5) stratification of following items by baseline symptoms (constipation/diarrhea): GSRS total score, GSRS subdomain scores, proportion of participants whose fecal properties are within normal range, defecation frequency, blood test biomarkers, and gut microbiota. The exploratory endpoints of this trial will be as follows: (1) blood, urine, and stool metabolomes (short, medium, and long chain fatty acids, amino acids, carbohydrates, and bile acids); (2) items other than nutrients evaluated in the secondary endpoints and items evaluated by the diabetes treatment satisfaction questionnaire (DTSQ) [17]; (3) items other than physical examination evaluated in the secondary endpoints; (4) items other than gut microbiota evaluated in the secondary endpoints; (5) change in lipopolysaccharide-binding protein; (6) subgroup analysis by age, sex, etc. Harm outcomes will also be evaluated based on various laboratory abnormalities and adverse reactions to the medication.

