### Data collection and management

#### Plans for assessment and collection of outcomes

The researchers will manage the data of the participants using the central registry number assigned by the data center. In this study, data on study participants reported by the researchers will be collected at each observation point using a case report form (CRF), survey forms (GSRS, BDHQ, and DTSQ), logbooks (defecation frequency, stool characteristics (Bristol scale score), and adherence to BBG9-1). We will use the average of the 1-week Bristol scale scores as the Bristol scale score. The survey forms of 12-week after the baseline examination and logbooks during the observation periods will be sealed using a special envelope and sent to the data center in such a way that the investigators or researchers cannot confirm the contents of the responses. The investigators or researchers will ensure that the survey forms and logbooks other than those answered and recorded by the research participants themselves are complete in order to ensure that the data recorded by the research participants (CRFs) are not lost or destroyed. If any data correction is necessary, the date and reason for the correction shall be recorded. Researchers shall confirm that all data, including the corrected data, are accurate and complete and shall ensure the quality of the data. For data submitted in the CRF, the data management staff will maintain a central registry of all data from the site.

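### Worsening of any endpoint is barred from being an adverse event, with no exception for clinically significant or serious worsening, so individual harms in bowel symptoms and laboratory values drop out of the adverse-event list

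*Protocol article*

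**What the plan says.** All references are to the Protocol article.

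- **The rule.** Reporting of adverse events and harms states that "if the data related outcomes, including primary endpoints, secondary endpoints and exploratory endpoints, worsens, it will not be treated as an adverse event".
- **The general definition, same section.** An adverse event is "Any unfavorable medical event that occurs to a research participant during the course of this study, including an exacerbation of previous illnesses".
- **The endpoints (Outcomes).** "The primary endpoint of this trial will be the change in the total GSRS score from baseline to follow-up examination". The secondary endpoints include "GSRS subdomain scores, fecal properties/Bristol stool form scale, defecation frequency, blood test biomarkers". The blood markers include "glucagon, HbA1c, fasting plasma glucose, C-peptide, AST, ALT, gamma-glutamyltransferase" and, at the end of the list, "triglycerides, blood urea nitrogen, and creatinine". Urinary albumin creatinine ratio and body weight are also secondary endpoints.
- **Harms (Outcomes).** "Harm outcomes will also be evaluated based on various laboratory abnormalities and adverse reactions to the medication".
- **Safety analysis (Statistical methods for primary and secondary outcomes).** Adverse events are listed by group in the safety population, with Fisher's test between groups if needed. No other safety analysis is stated.
- **Serious adverse events.** These have their own definition, based on seriousness criteria and a causal relation to the study drug. It does not repeat the endpoint exclusion.

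**The concern.** An oral probiotic given to people with diarrhoea or constipation is most likely to do harm, if it does any, through bowel symptoms. These are exactly the variables that the trial uses as endpoints. Most of the routine liver, kidney and metabolic values are endpoints too. A rule that keeps endpoint worsening out of the adverse-event record, whatever its size, removes such events from the place where a reader looks for them. A later statement that no gastrointestinal or laboratory adverse events occurred could then be true by definition. Investigators also know the treatment arm, because the trial is open-label. Two conflicting definitions of an adverse event invite sites to record the same event differently.

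**Working it through.** No sample-size or power figure bears on this point. The check is a comparison of the sections, with one short calculation.

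**1. What the exclusion covers.** The secondary endpoints name these blood markers: total bile acid, glycoalbumin, GLP-1, GIP, glucagon, HbA1c, fasting plasma glucose, C-peptide (8); AST, ALT, gamma-glutamyltransferase (3); total, HDL and LDL cholesterol, triglycerides (4); blood urea nitrogen, creatinine (2). Total: 8 + 3 + 4 + 2 = 17. To these are added the GSRS total and subdomain scores, stool form, defecation frequency, urinary albumin creatinine ratio and body weight. Lipopolysaccharide-binding protein and the metabolomes are exploratory endpoints. Every blood analyte named in the section on biological specimens is therefore an endpoint of some rank.

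**2. Whether the rule has a limit.** It applies to all three ranks of endpoint. It has no clinical-significance threshold and no exception for worsening that needs treatment, ends participation or meets a seriousness criterion.

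**3. Where an individual worsening would appear.** Under the rule it does not enter the adverse-event list. It does enter the endpoint comparison, but t-tests and rank tests respond to group shifts. With the planned 45 evaluable participants per arm, a rise of size R in one participant moves the arm mean by R/45, about 2.2% of R (1/45 = 0.022). A log-transformation or rank test, which the plan allows for non-normal data, reduces its influence further. Participants who worsen and stop may have no week-12 value at all: data are collected only up to discontinuation (Data management) and missing values are not imputed. They could then be absent from both the list and the comparison.

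**4. Sections side by side.**

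| Section | What it implies | Under the exclusion |
|---|---|---|
| Reporting of adverse events, definition | Exacerbation of an existing illness is an adverse event; all participants enter with diarrhoea or constipation | Worsening of the measured bowel symptoms is not |
| Reporting of adverse events, complications | Worsening microvascular complications are adverse events | Urinary albumin creatinine ratio is a secondary endpoint, so its worsening is not |
| Outcomes, harms | Laboratory abnormalities are a basis for judging harm | No blood analyte named in the article can be reported as an adverse event for worsening |
| Criteria for discontinuing | HbA1c of 10% or more ends observation | The HbA1c rise that ends observation is not an adverse event |
| Serious adverse events | A related symptom or illness meeting a seriousness criterion is reported | Not stated which rule prevails if the symptom is also an endpoint |

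The first three rows are conflicts. The last two are gaps in how the rules fit together.

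**The case against.** The principle behind the rule is sound. Everyone enters with bowel symptoms, and counting each unfavourable move in a score or in one of 17 markers as an adverse event would duplicate the efficacy analysis and fill the list with noise. The excluded item can also be read as measured data rather than clinical events. On that reading, laboratory harms are judged from the laboratory data and adverse events from clinical reports. This supports keeping trivial fluctuation out of the list. It does not support a rule without any carve-out, and the text does not state the narrower reading.

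A reader might infer more than the document supports, in four ways:

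- *That these harms vanish from the trial's data.* They do not. The values are collected in both arms and compared as endpoints, so a shift across an arm would be visible. What is lost is the individual event in the adverse-event list.
- *That symptom worsening has no route to the investigator.* The week-12 forms and the logbooks are "sent to the data center in such a way that the investigators or researchers cannot confirm the contents of the responses", but participants can report symptoms directly and adverse events are recorded throughout observation. Sealing has no bearing on blood tests. The difficulty is that a symptom reported directly still meets the exclusion.
- *That a hospitalisation for diarrhoea would go unreported.* The serious-event definition does not repeat the exclusion, so this is unclear rather than established.
- *That the whole safety profile is excluded.* Allergic reactions, infections and other illnesses that are not endpoints remain reportable, and several of the 17 markers are mechanistic rather than safety measures.

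Laboratory safety tables may also be in the full protocol or the analysis plan, so their absence from the article is not in itself a fault.

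**Conclusion.** The point holds as a defect in a stated rule. Followed as written, clinically significant worsening in an individual's bowel symptoms, or in nearly all the named laboratory values, stays out of the only stated safety analysis. The rule contradicts the adverse-event definition in its own section and the harm outcomes in Outcomes. It leaves the handling of serious endpoint worsening undefined. The number of events affected cannot be derived from the document, and the exclusion applies to both arms. The primary estimate, sample size and randomisation are unaffected. The conclusion assumes that sites apply the sentence literally and that the full protocol has no exception that the article omits. If it has one, the article's wording should be brought into line with it.

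**What to change.** Delete the sentence, or limit it to endpoint changes that are not clinically significant. State that endpoint worsening is recorded as an adverse event, or as a serious one, when it is clinically significant, leads to treatment or discontinuation, or meets a seriousness criterion. The sponsor's clinicians should set the significance thresholds. State expressly that the serious-event rules apply to endpoint variables too. Tabulate individual laboratory abnormalities by arm, unless the analysis plan already does so; the values are being collected anyway. Reconcile the sections on discontinuation criteria, Outcomes, statistical methods, and adverse and serious adverse event reporting.

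The cost is an amendment to the wording, more adverse-event entries for sites and the data center, and somewhat less favourable reported rates. No extra visits, tests or participants are needed. If participants have already been followed under the present rule, their laboratory values can be reviewed from existing data, but symptom events not recorded at the time may not be recoverable.

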#### Frequency and plans for auditing trial conduct

The auditing trial conduct will be conducted by EviPRO, Inc., in accordance with the procedures.

#### Plans for communicating important protocol amendments to relevant parties (e.g., trial participants and ethical committees)

Important protocol modifications that may have an impact on the potential benefit for the participant, the safety of participant, or the conduct of the study, will be communicated to the trial registries, ethical committee, sponsor, and trial participants.

#### Dissemination plans

Before enrolment of the first study participants, the study plan will be registered and published in the database maintained by the Ministry of Health, Labour, and Welfare (Japan Registry of Clinical Trials/jRCT). The progress of the research will be updated as appropriate, and completion of the research will be reported without delay. All data and results obtained in this study will belong to the investigators and researchers. These results will be published in scientific journals.

## Discussion

This randomized, parallel-group, comparative study explores the effects of the probiotic BBG9-1 on the symptoms of diarrhea or constipation in patients with T2DM.

Previous studies have revealed that many patients with diabetes have gastrointestinal diseases such as diarrhea and constipation [2–4]. In addition, medications for diabetes increase the risk of gastrointestinal complications [5]. Furthermore, recent studies have revealed a relationship between gastrointestinal complications and gut microbiota [6]. Therefore, treatment to improve abdominal symptoms, such as diarrhea and constipation, through the improvement of the gut microbiota is needed.

Recent studies have revealed that probiotics containing BBG9-1 improve the balance of gut microbiota and result in improved gastrointestinal complications in both animal models [19] and humans [15]. However, because previous human studies were conducted in a single group without a control group, further investigation is needed to clarify the efficacy and mechanism of BBG9-1 in patients with T2DM having constipation or diarrhea.

This is a randomized, parallel-group, comparative study with a control group to evaluate the effect of the probiotic BBG9-1 on improving abdominal symptoms in patients with T2DM. The results of this study will clarify the efficacy of the probiotic BBG9-1 in the treatment of diarrhea or constipation in patients with T2DM.

## Abbreviations

BBG9-1: *Bifidobacterium bifidum* G9-1
T2DM: type 2 diabetes mellitus
GSRS: Gastrointestinal Symptom Rating Scale
ALT: alanine aminotransferase
AST: aspartate transaminase
CRF: case report form
FAS: full analysis set
PPS: per protocol set
SAE: serious adverse event
